### Statistical Power

Power analyses and sample size calculations were based on the primary outcome of viral suppression (aim 2). No viral load data are available for transgender people in South Africa disaggregated from other key populations. The only South African data that includes transgender women and uses the current nationally recommended threshold for viral suppression includes cisgender men who have sex with men. Nonetheless, the study found a viral suppression rate of 47% [101]. One study of transgender people receiving TG-DSD in South Africa found that those on GAHT were 3 times more likely to be virally suppressed compared to transgender people who are not on GAHT [49]. This suggests an effect size of at least 20%. We consider an effect size as low as 15% to be clinically significant.

On the basis of the aforementioned data and clinical experience, we anticipate that current viral suppression rates will be approximately 65% at baseline, rising to 85% at 12 months among TG-DSD participants, and approximately 61% at baseline, rising to 66% at 12 months among SSD participants. This 20% difference from baseline to 12 months for TG-DSD participants and 5% difference from baseline to 12 months for SSD participants represents a difference in the absolute change in viral suppression rates of 15%. Using *r*=1, α=.05, power of 1− β=.80, and p_1_=viral suppression in the SSD and p_2_=viral suppression in the TG-DSD group and difference of p_2_ – p_1_=.15, the minimum sample per group will be 172 for both TG-DSD and SSD, for a total minimum sample size of 344. Adjusting for loss to follow-up of approximately 12%, a sample of ≥200 in each group, for a total of ≥400 transgender people on ART, provides adequate statistical power for planned analyses.

Loss to follow-up is a challenge for any longitudinal study. We will make every effort to minimize loss to follow-up by collecting multiple forms of contact, reaching out monthly to update contacts, collecting data in the field as well as the study site, and providing remuneration for study participation. We are enrolling a larger sample size than required by the power calculations to allow for potential loss to follow-up without loss of statistical power.

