	**Client**			
		IDIs with transgender participants	Tell me about your experience receiving care at the site.	
		Survey with transgender participants	Intersectional stigma scale by Scheim and Bauer [77], Psychological Gender Affirmation scale by Sevelius et al [78], and GAHT use by self-report.	
		Laboratory test with transgender participants	HIV RNA level by serum analysis (for transgender participants on ART) and tenofovir level by DBS^i^ (for transgender participants on PrEP)	

^a^GAHT: gender-affirming hormone therapy.

^b^ART: antiretroviral therapy.

^c^PrEP: pre-exposure prophylaxis.

^d^KII: key informant interview.

^e^AIM: Acceptability of Intervention Measure.

^f^IAM: Intervention Appropriateness Measure.

^g^FIM: feasibility of intervention measure.

^h^IDI: in-depth interview.

^i^DBS: dried blood spot.

Qualitative interview (KII and IDI) recordings will be transcribed and translated into English. The transcripts, field notes, and narrative summaries will be uploaded into qualitative data management software, Atlas.ti (ATLAS.ti Scientific Software Development GmbH), to facilitate analyses. During regularly scheduled meetings, the study team will review field notes, transcripts, and summaries; discuss emerging themes; and revise interviewing and coding strategies, as needed.

Statistical analysis of quantitative data will be performed using Stata (StataCorp) and MPlus (Muthén & Muthén). Data exploration of key variables will be conducted to assess for implausible values and determine whether statistical assumptions (eg, normal distributions of data) for planned statistical analyses are satisfied. Categorical variables will be reported as frequencies and percentages, with means and SDs or medians and IQRs reported for continuous variables. Patterns of missing data will be examined, including testing for differences between participants with and without missing data. A series of sensitivity analyses will be conducted to evaluate the robustness of conclusions drawn from the primary models to departures from the missing at random assumption by comparing the magnitude of the primary effect. In the rare situation that >10% missing data is observed, we will use multiple imputation, as appropriate. We will specify 2-sided tests, .05 significance level (α=.05), and compute 95% CIs throughout.

### Qualitative Data Analysis for Aim 1

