We will use quantitative methods to evaluate the effectiveness of TG-DSD for viral suppression and prevention-effective adherence and to assess stigma and GAHT use as potential mediators. As noted earlier, our first hypothesis is that rates of viral suppression are more likely to increase among transgender people on ART at TG-DSD sites than among transgender people on ART at SSD sites over the 12-month study period.

The primary outcome measure is the proportion of transgender people on ART with viral suppression (HIV RNA <50 copies/mL). Descriptive analyses will summarize HIV viral suppression comparing participants at TG-DSD versus SSD sites as well as by gender identity at baseline and 12 months. Percent distributions will be computed for categorical variables and means, ranges, SDs, medians, and IQRs will be presented for continuous variables stratified by attendance at TG-DSD versus SSD sites. The primary estimate for this aim is the absolute difference in the change in proportion of virally suppressed during the study period between participants at TG-DSD sites and those at SSD sites. A difference-in-difference (D-i-D) analysis will be conducted to account for anticipated differences between groups at baseline (TG-DSD vs SSD). In addition, we will compare differences at 12 months considering baseline values to enhance the robustness of the estimators of the differences in the 2 groups.

A mixed-effects binomial model will be fit, where the binary viral load suppression status of each client is regressed on fixed effects for time (baseline vs 12 months), TG-DSD versus SSD site, the time by site model interaction, and client-level covariates (age and gender identity). In addition, random intercepts for each of the sites will be included in the model to account for within-site correlation. The D-i-D estimator is the estimated regression coefficient for the time by service delivery model interaction term. All models will account for clustering and be adjusted for relevant confounders in baseline covariates.

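### The 172 per group is sized for one two-proportion comparison, not for the primary difference-in-difference, so 80% power is not established for the primary analysis

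*Protocol article*

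**What the plan says.** Protocol article, Statistical Power. The section cites one earlier South African figure: "the study found a viral suppression rate of 47"%. It then expects TG-DSD suppression to start from 65%, with the other three rates given as "rising to 85% at 12 months among TG-DSD participants, and approximately 61% at baseline, rising to 66% at 12 months among SSD participants", and describes the 15 points as the difference between the two absolute changes (20 minus 5). The calculation uses "α=.05, power of 1− β=.80" and "difference of p_2_ – p_1_=.15", with p1 and p2 described as suppression in the standard (SSD) and transgender-specific (TG-DSD) groups and no values given for either. The result is that "the minimum sample per group will be 172 for both TG-DSD and SSD, for a total minimum sample size of 344". After about 12% loss this becomes 200 per group, "for a total of ≥400 transgender people on ART", which the section calls adequate for the planned analyses.

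Protocol article, Data Analysis for Aim 2. "The primary estimate for this aim is the absolute difference in the change in proportion of virally suppressed during the study period", compared between the two kinds of site. It is tested through the time-by-model interaction in a mixed-effects binomial model with random site intercepts, and all models are to allow for clustering.

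Protocol article, Overall Approach to Data Analysis. "We will specify 2-sided tests, .05 significance level (α=.05), and compute 95% CIs throughout".

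**The concern.** The 15 points is defined as a difference between two changes but entered as a difference between two proportions. A single comparison of two groups carries two sampling variances. A D-i-D carries four, reduced by the correlation between each person's baseline and 12-month results. The section states no such correlation. It also makes no allowance for changes that differ from site to site, although the analysis is to account for clustering across 4 sites per model.

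This is the only sample-size justification for the primary outcome. If the D-i-D turned out null, a reader relying on the section would credit the study with an 80% chance of detecting a 15-point effect, and the calculation does not show that.

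**Working it through.** **Inputs from the article.** Two-sided α = 0.05; power 0.80; equal groups; difference 0.15; rates 0.65 to 0.85 (TG-DSD) and 0.61 to 0.66 (SSD); loss about 12%; 4 + 4 sites.

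**Inputs not in the article, assumed over a range.** Within-person correlation ρ from 0 to 0.5. SD of the true change between sites (τ) from 0 to 5 points. Reference distribution normal, or t with 8 − 2 = 6 df.

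**1. Reproducing 172.** Pooled two-proportion formula, no continuity correction, with p̄ = (p1 + p2)/2:

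n = [1.96·√(2p̄(1−p̄)) + 0.84·√(p1(1−p1) + p2(1−p2))]² / (p2 − p1)²

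| p1 vs p2 | n per group |
|---|---|
| 47% vs 62% | 171.8, so 172 |
| 61% vs 76% | 149.4, so 150 |
| 65% vs 80% | 137.9, so 138 |
| 66% vs 81% | 134.7, so 135 |
| 66% vs 85% (the anticipated 12-month rates) | 79.2, so 80 |

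Among the rates in the section, only 47% gives 172. This is an inference: p1 of 37%, 38% or 48% with the same 15-point gap also rounds up to 172. The loss step is sound: 172/0.88 = 195.5, so 196, and 200 × 0.88 = 176 completers.

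**2. Variance of the absolute D-i-D, per participant per group.**

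Sum of p(1−p) over the four rates: 0.2275 + 0.1275 + 0.2379 + 0.2244 = 0.8173.

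Covariance terms: √(0.2275 × 0.1275) = 0.1703 and √(0.2379 × 0.2244) = 0.2311, together 0.4014.

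V(ρ) = 0.8173 − 2ρ × 0.4014; SE = √(V/n); power = Φ(0.15/SE − 1.96); n for 80% = V × 7.849/0.0225.

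Examples at n = 172: for ρ = 0, SE = √(0.8173/172) = 0.0689 and power = Φ(0.22) = 59%. For ρ = 0.4, V = 0.4962, SE = 0.0537 and power = Φ(0.83) = 80%.

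| ρ | V | Power, 172 | Power, 176 | n per group for 80% |
|---|---|---|---|---|
| 0 | 0.8173 | 59% | 60% | 286 |
| 0.2 | 0.6568 | 68% | 69% | 230 |
| 0.3 | 0.5765 | 74% | 75% | 202 |
| 0.4 | 0.4962 | 80% | 81% | 174 |
| 0.5 | 0.4159 | 86% | 87% | 146 |

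The smallest ρ that reaches 80% is about 0.40 with 172 completers and 0.39 with 176. At ρ = 0, 286 completers correspond to 286/0.88 = 325 enrolled per group.

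**3. Site-by-time variation.** A stable site effect cancels in a within-site change, so an inflation based on the cross-sectional intraclass correlation would overstate the penalty. What remains is variation between sites in the change itself: SE² = V/n + 2τ²/4. At n = 172:

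| ρ | τ | Power, normal | Power, t on 6 df |
|---|---|---|---|
| 0 | 0 | 59% | 45% |
| 0 | 5 points | 49% | 37% |
| 0.4 | 0 | 80% | 65% |
| 0.4 | 3 points | 74% | 58% |
| 0.4 | 5 points | 65% | 50% |
| 0.5 | 0 | 86% | 72% |
| 0.5 | 5 points | 70% | 55% |

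**The case against.** The strongest reply is that nothing here shows power to be below 80%. The article gives neither ρ nor τ. With ρ of about 0.4 or more, no site-by-time variation and a normal reference, the planned 176 completers reach 80%. The largest ρ possible with rates of 65% and 85% is 0.57, so 0.4 is attainable. This stands: a reader might infer that the study is underpowered, and the documents do not support that.

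Scale also matters. The estimator is described as an interaction coefficient in a binomial model. If the link is logit, which is not stated, 80% needs 203 per group at ρ = 0, and 172 gives 73% rather than 59%. The absolute figures are used here because the article names the absolute difference as its primary estimate.

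It is also tempting to say that the written model assumes ρ = 0, because only site intercepts are named. An article may condense this, and it also says that all models account for clustering. So ρ = 0 belongs in the range without being a settled property of the model. Likewise, the 6-df results rest on a reference distribution that the article does not specify.

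Finally, the four anticipated rates are not idle, since they supply the 15 points. Confidence intervals are promised throughout, so a null result can be read from its interval. The supporting 12-month comparison (66% versus 85%) would have about 99% power at 172 per group, taking participants as independent with no site effect. None of this turns the 172 into a D-i-D calculation.

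**Conclusion.** The point holds as a mismatch between formula and estimand. The arithmetic of 172 is right for a one-time comparison consistent with 47% versus 62%, but it cannot be reproduced from the section's anticipated rates and is not a calculation for the primary absolute D-i-D. The stated 80% is therefore not established.

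At 172 completers per group the supportable range is 59% to 86% for ρ from 0 to 0.5, assuming the four stated rates, no site-by-time variation and a normal reference. Relaxing either of the last two assumptions lowers every figure. Whether true power lies above or below 80% depends on inputs the article does not give. That p1 was actually set to 47% is likely but not documented.

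**What to change.** Keep 200 per group. Replace the two-proportion calculation with a power table for the absolute D-i-D at the four stated rates and 176 completers per group. Cross within-person correlation (0, 0.2, 0.3, 0.4, 0.5) with a between-site SD of change from 0 to 5 points. Name the reference distribution (normal or t with 6 df), and label correlation and site SD as assumptions. Limit the statement that power is adequate to the combinations that reach 80%. If the 172 is kept for the record, state the p1 and p2 behind it and say that it refers to a single-time comparison.

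The cost is a rewritten paragraph and one table. The stated power becomes less favourable. No participants are added, and the estimand and model are unchanged.

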## Results

The Jabula Uzibone study enrollment began in January 2024. As of July 31, 2024, a total of 593 transgender participants have been enrolled: 348 are living with HIV and 245 are HIV negative. We anticipate baseline enrollment will be complete by August 31, 2024, and the final study visit will take place no later than August 2025.

## Discussion

### Expected Findings

We anticipate that the Jabula Uzibone study will demonstrate that TG-DSD is associated with higher rates of viral suppression and prevention-effective adherence compared with SSD. Furthermore, we expect qualitative and quantitative results to indicate that these associations are mediated by gender affirmation and stigma reduction. Importantly, we expect to find that broader implementation of key aspects of TG-DSD models, including cost, are feasible, acceptable, and appropriate.

Prior studies of DSD models support their effectiveness for improving retention in care and viral suppression for people living with HIV in sub-Saharan Africa [102]. However, the largest systematic review assessing DSD implementation barriers and facilitators excluded key populations [103]. This study will fill the critical gap in data on DSD for transgender people, a key population, as well as provide the first data on use of DSD for HIV prevention services.

### Strengths and Limitations

This study is limited by its nonrandomized, observational nature. As TG-DSD is already being offered at Wits RHI sites in South Africa, sites cannot be randomized. While randomized controlled trials (RCTs) are considered the highest standard of scientific evidence, an RCT is not feasible in this situation. If an RCT were possible, it would run the risk of producing findings that cannot be replicated in less controlled settings. Jabula Uzibone will generate rich data on implementation strategies and intervention effectiveness in real-world conditions.

Assessment of prevention-effective adherence among participants who are HIV negative and not prescribed PrEP relies on self-reported sexual behaviors. Recall and social desirability bias may affect the accuracy of self-report. Despite this limitation, our choice to measure overall prevention-effective adherence (rather than limiting measures to tenofovir levels among participants on PrEP) allows for broader applicability of findings to the real lives of transgender people whose sexual behavior and indication for PrEP shift over time [23].

### Conclusions

In addition to dissemination in scientific journals and relevance conferences, results from this study will be shared directly with both transgender community organizations and the National Department of Health in South Africa. Jabula Uzibone will provide actionable data to inform HIV policies and health facility practices in South Africa and generate the first evidence for implementation of TG-DSD in sub-Saharan Africa. Study findings also may inform how other countries could use TG-DSD strategies to increase engagement of transgender people in care and advance global progress toward HIV elimination goals.

## Appendix

Multimedia Appendix 1 Peer review report from the National Institutes of Health.

## Abbreviations

AIM: Acceptability of Intervention Measure
ART: antiretroviral therapy
D-i-D: difference-in-difference
DSD: differentiated service delivery
FIM: feasibility of intervention measure
GAHT: gender-affirming hormone therapy
IAM: Intervention Appropriateness Measure
IDI: in-depth interview
KII: key informant interview
PrEP: pre-exposure prophylaxis
RCT: randomized controlled trial
RE-AIM: Reach, Effectiveness, Adoption, Implementation, and Maintenance
REDCap: Research Electronic Data Capture
SSD: standard service delivery
TG-DSD: transgender-specific differentiated service delivery
UNAIDS: Joint United Nations Programme on HIV and AIDS
WHO: World Health Organization
